### Timeline

Recruitment began in August 2019, and the intervention period will end in December 2020. Table 1 provides the schedule of enrollment, intervention, and assessment.

### Data collection and management

Each center will designate a full-time researcher, and data collection will be performed in a dermatology clinic using a unified data collection system (provided by Nanjing Ningqi Medical Technology Co., Ltd. Data Management Center, Nanjing, China). With the exception of the DLQI, R-QoL, and VAS, the evaluation indicators will be completed by data collectors. All data collectors will be trained to implement the PASI and other scales.

### Data monitoring and auditing

This study will establish the Data and Safety Monitoring Board (DSMB), which is composed of three members, including an acupuncturist, a dermatologist, and a statistician. All members must declare any conflict of interest during the trial. The DSMB will monitor the progress of the trial and review the safety and quality of the data. They will meet quarterly to review any adverse events and safety issues. All adverse events and severe adverse events will be reported to the main researchers, IRB, and DSMB within 24 hours. The primary investigator will receive the interim results and make the final decision regarding study termination.

### Statistical analysis

In this study, quantitative variables (PASI, DLQI, R-QoL, VAS) with normal distributions will be described as means and standard deviation; non-normal distribution will be summarized as median and interquartile range. Quantitative variables will be compared using a Student *t* test for normally distributed variables and the Wilcoxon rank-sum test for non-normally-distributed variables. Qualitative variables (sex, age) will be summarized as frequency and proportions, and the chi-square or Fisher exact test will be used to test the differences between qualitative variables. Quantitative variables with repeated measures will be applied with general linear models. *P* < 0.05 will be considered statistically significant. All statistical analyses will be performed with SAS version 9.4 statistical package (SAS Institute Inc., Cary, NC, USA). The measurer will be blinded to the results.

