### Recruitment

We plan to recruit 122 patients with plaque psoriasis for this study. They will be evenly distributed among six hospitals using fixed enrollment. Recruitment will occur at the Yueyang Hospital of Integrated Traditional Chinese and Western Medicine (Shanghai, China), Shaanxi Traditional Chinese Medicine Hospital (Shaanxi, China), First Affiliated Hospital of Heilongjiang University of Traditional Chinese Medicine (Heilongjiang, China), the Affiliated Hospital of Jiangxi University of Traditional Chinese Medicine (Jiangxi, China), Hospital of Traditional Chinese Medicine, Xinjiang Medicine University (Xinjiang, China), and Shijiazhuang Hospital of Traditional Chinese Medicine (Shijiazhuang, China). Eligible recipients will be recruited via social media, word of mouth, and dermatology outpatient clinics at local hospitals. Each hospital will designate three dermatologists for patient recruitment and one physician (dermatologists trained and qualified to perform moving cupping) for moving cupping treatment. Patients will be informed and asked to provide written informed consent prior to study commencement. Figure 1 presents a flowchart of participant enrollment and analysis throughout the course of the trial. Researchers will obtain recipient consent prior to trial participation. All potential and enrolled recipients’ personal information will be recorded, kept in a secure folder, and made accessible only to the researchers in order to protect their privacy.

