### Randomization, allocation, and blinding

Once eligibility is confirmed and consent is obtained, participants will be block-randomized using a non-stratified, permuted block with varying lengths (*n* = 6 blocks; patient distribution = 1:1) for each arm/group. Independent statisticians will provide computer-generated random sequences. Distribution will be conducted by a central web-based interactive randomization service system. When a participant is eligible, the researcher who conducts the random grouping will need to log onto the website to view the grouping situation of the participant. Due to the nature of moving cupping, it is not possible to blind the operating physician involved in treatment application. To ensure blinding, we will use a placebo cup to simulate the treatment of moving cupping and shield the patient’s eyes with a black opaque eye mask. The treatment device will be of the same size and material as well, and the treatment method will maintain consistent frequency and intensity, but with no adsorption force. Each hospital will designate one operating physician who is a dermatologist trained to perform moving cupping therapy and has obtained the relevant operational qualifications. The operating physician will not participate in the statistical analysis, and the treatment plan and grouping will be known only by the statistical analyst.

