### Missing data

The possibility of loss to follow-up has been considered and will be calculated as a part of the sample size estimation. The dropout rates and reason will be recorded. In addition, we will account for other types of randomly missing data by treating dropouts as non-success or non-survival using the intention-to-treat principle.

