This study will be the first placebo-controlled study of moving cupping for the treatment of plaque psoriasis with multiple centers, double-arm parallel groups, and a single-blind RCT. Furthermore, the study has several advantages. The first is that it will use a placebo control to exclude the placebo effect, reduce the risk of bias, and define the clinical efficacy of moving cupping for the treatment of plaque psoriasis. The second advantage is that, because of the large land area of China, the study will include a total of six hospitals in different regions, thus including various ethnic and socioeconomic populations. As such, its experimental design will increase the generalizability of the trial outcomes. However, this study also has some limitations. Due to the particularity of moving cupping therapy, it is difficult for different operators to maintain the same strength when moving the cup. Furthermore, because different cup sizes will be selected for the different treatment sites, adsorption forces will be inconsistent. All of these limitations may lead to the risk of bias. The placebo cupping therapy method has been used previously in only two clinical trials [37, 38]. Although the moving cupping placebo lacks absorption during treatment, we found that most patients do not understand the specific operation of the treatment method; therefore, they cannot distinguish between the moving cupping placebo and moving cupping. Patients were blinded to whether they are accepting real or placebo cupping. In conclusion, this study aims to verify whether moving cupping therapy is effective for treating plaque psoriasis. We also hope to provide a safe and effective treatment for plaque psoriasis through this study.

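### The quantitative outcomes are compared with unadjusted t or Wilcoxon tests that leave the collected baseline unused, and no rule covers a missing score

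*Protocol article*

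**What the plan says.** All references are to the protocol article.

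- **Two-group tests, quantitative outcomes** (Statistical analysis; PASI, DLQI, R-QoL and VAS are listed): "Quantitative variables will be compared using a Student *t* test for normally distributed variables and the Wilcoxon rank-sum test for non-normally-distributed variables".
- **Repeated measures** (same section): "Quantitative variables with repeated measures will be applied with general linear models". SAS 9.4 is named, but no procedure, model terms, covariance structure or handling of missed visits.
- **Qualitative variables** (same section): "the chi-square or Fisher exact test will be used to test the differences between qualitative variables". This is the only named test that fits the primary outcome, the proportion with a PASI reduction of at least 75% at week 4 (Primary parameters).
- **Missing data**: dropouts count as non-success or non-survival, "using the intention-to-treat principle".
- **Visits** (Table 1): PASI and VAS are recorded at allocation and at weeks 1, 2, 3, 4, 6 and 8; DLQI at allocation and weeks 1 to 4.
- **Hospital**: patients are spread evenly over six hospitals, and allocation is "block-randomized using a non-stratified, permuted block with varying lengths".

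**The concern.** Each quantitative outcome has a baseline value and four to six later values. A t or Wilcoxon comparison of the arms cannot carry the baseline as a covariate, so information already collected is left out of the test. Which of the two tests is used also depends on how the trial's own data look.

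The general linear model could use the baseline, but the article does not say whether it does, or what happens to a patient who misses a visit. That second point matters because the one missing-data rule is written for success or failure. It settles a missing responder status and gives no number for a missing PASI, DLQI or VAS score. Patients may leave for worsening, adverse events or non-compliance (exit criteria under Criteria), so some missing scores will probably be related to outcome.

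At stake are the precision of the quantitative comparisons and the set of patients they describe. Continuous PASI matters here because the objectives state the hypothesis as a greater fall in PASI than with placebo.

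**Working it through.** **Inputs from the article.** Responder rates 62.1% and 35.3%, two-sided alpha 0.05, power 0.80, 51 per arm, 20% loss, 61 per arm, 122 in total (Sample size); the visit schedule (Table 1).

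**Inputs not in the article, assumed.** A baseline-to-follow-up correlation rho of 0.3 to 0.8, with equal variance at both times.

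**The plan's own figure.** The printed formula gives

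n = (0.621 × 0.379 + 0.353 × 0.647) / 0.268² × (1.960 + 0.842)² = 0.4638 / 0.0718 × 7.849 = 50.68, so 51 per arm.

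Then 51 × 1.2 = 61.2, taken as 61, which gives 122. The figure reproduces. It rests on two proportions, so the analysis of the quantitative outcomes does not alter it.

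**Step 1: precision.** Let s² be the outcome variance. The variance behind each comparison is s² for follow-up scores, 2s²(1 − rho) for change scores and s²(1 − rho²) with baseline as covariate. The ratio of adjusted to unadjusted variance is therefore 1 − rho² against follow-up scores and (1 + rho)/2 against change scores. Both are shown because the article does not say which score is tested, and its abstract speaks of comparison with baseline values.

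If the adjusted analysis had 80% power, the unadjusted test would have power Φ(2.802 × √ratio − 1.960). At rho = 0.5 this is Φ(2.802 × 0.866 − 1.960) = Φ(0.466) = 68%.

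| rho | Ratio v follow-up | Variance cut | Unadjusted power | Ratio v change | Variance cut | Unadjusted power |
|---|---|---|---|---|---|---|
| 0.3 | 0.91 | 9% | 76% | 0.65 | 35% | 62% |
| 0.5 | 0.75 | 25% | 68% | 0.75 | 25% | 68% |
| 0.7 | 0.51 | 49% | 52% | 0.85 | 15% | 73% |
| 0.8 | 0.36 | 64% | 39% | 0.90 | 10% | 76% |

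The formulas are for the t test. They are only a guide for the Wilcoxon test, which cannot carry a baseline covariate either.

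**Step 2: missing scores.** The non-success rule keeps every dropout in the week-4 responder analysis, so that analysis loses nobody. For a continuous score the rule assigns nothing. If, and only if, the repeated-measures model were fitted to complete cases, the planned loss would leave 122 × 0.8 = 97.6, about 98 patients. The standard error would rise by 1/√0.8 = 1.12, and 80% power would become Φ(2.802 × 0.894 − 1.960) = Φ(0.546), about 71%.

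**Step 3: hospital.** For a quantitative outcome, adjusting for hospital removes roughly the between-hospital share of variance: 1% to 10% for an assumed intraclass correlation of 0.01 to 0.10. For the responder outcome, simulation compared the chi-square test with a hospital-stratified Mantel-Haenszel test. Stratifying changed power by about +3 to +4 points at a between-hospital log-odds SD of 1.0, by 0 to −2 at 0.5, and by −1 to −2 with no hospital effect.

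**The case against.** The strongest reply is that nothing here is an error. Two-group tests without covariates are valid under randomization. A journal article may leave model terms, covariance structure and estimation method to a full protocol or analysis plan, and the general linear model may already contain baseline. The gain also rests on a correlation that the article does not give.

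Much of this stands, and it rules out several stronger readings that a reader might infer:

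- **That incomplete patients are dropped.** No sentence says so. Listwise deletion belongs to one way of fitting a repeated-measures general linear model. The article names only SAS 9.4, which also fits mixed models.
- **That the analysis conflicts with intention-to-treat.** For the primary outcome it does not, because dropouts are kept as non-successes. For continuous scores a conflict would arise only under a complete-case fit. What the text does show is that its rule does not reach those scores.
- **That baseline and hospital are ignored throughout.** They are absent from the named two-group tests, but neither included in nor excluded from the general linear model.
- **That hospital must be adjusted for, or allocation restratified.** Hospital is not a randomization stratum, so the analysis need not carry it, and chance imbalance between hospitals is already covered by the test's error rate. The Discussion does concede that "it is difficult for different operators to maintain the same strength when moving the cup". Since the sham cup has no suction, that would mainly make the treatment effect differ between hospitals, which a hospital main effect does not correct.

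The reply does not reach the choice of test. The t and Wilcoxon tests are named outright, so this is not merely a detail left for later.

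**Conclusion.** The point holds as a matter of efficiency and missing-data handling for the quantitative outcomes. The named comparisons leave out a baseline that is collected, and the missing-data rule has no meaning for a continuous score.

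The gain from adjustment depends on the unknown correlation and on which score is tested. It is 25% of the variance on either scale at 0.5. As the correlation rises, the gain grows against follow-up scores and shrinks against change scores. The loss to about 98 patients is a conditional risk and not something the plan states.

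The validity of the tests, the sample size and the binary primary analysis are not called into question. The change is worth making because it costs little, but the trial's main conclusion does not depend on it.

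**What to change.** **Quantitative outcomes.** Replace the normality-selected t or Wilcoxon comparison with a likelihood-based mixed model for repeated measures. Include baseline value, visit, arm and arm-by-visit, with hospital as an optional term. Use all randomized patients with any post-baseline value, so that visits before an exit still contribute. Report the week-4 difference between arms with its confidence interval. State that missing scores are handled by this model, so that the non-success rule is clearly confined to responder outcomes.

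**Primary outcome.** Keep the non-success rule for PASI-75. Hospital adjustment there is optional, and Step 3 shows no gain unless hospitals differ greatly.

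**Randomization.** Leave the scheme unchanged mid-trial. With one unblinded operator per hospital, blocks within hospital would make later allocations easier to predict.

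**Cost.** A few sentences and minor programming in the package already named. The downside is that the model assumes scores are missing at random given the recorded data, which should be stated because some exits may be related to outcome.

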## Methods

### Study design

The proposed study is designed as a prospective, multicenter, two-arm parallel group, single-blind RCT. Patients with plaque psoriasis will be randomly assigned to the treatment group (moving cupping) or the placebo group (sham moving cupping). Eligible participants will receive 4 weeks of treatment and a total of 8 weeks of follow-up (Table 1).

**Table 1 Tab1:** Study schedules of enrollment, intervention, and assessment

	Study period							
	Enrollment	Allocation	Treatment period				Follow-up period	
Time point	-week_1_	0	week_1_	week_2_	week_3_	week_4_	week_6_	week_8_
Enrollment								
Eligibility screen	**×**							
Informed consent	**×**							
List other procedures	**×**							
Allocation		**×**						
Interventions:								
Basic treatment plus moving cupping therapy								
Basic treatment plus moving cupping placebo								
Assessments:								
PASI	**×**	**×**	**×**	**×**	**×**	**×**	**×**	**×**
BSA	**×**	**×**	**×**	**×**	**×**	**×**	**×**	**×**
PGA	**×**	**×**	**×**	**×**	**×**	**×**	**×**	**×**
DLQI		**×**	**×**	**×**	**×**	**×**		
VAS		**×**	**×**	**×**	**×**	**×**	**×**	**×**
TCMSSS		**×**	**×**	**×**	**×**	**×**		
Vital signs	**×**	**×**	**×**	**×**	**×**	**×**		
Routine blood test	**×**					**×**		
Blood biochemical test	**×**					**×**		
Routine urine test	**×**					**×**		
Food allergen test	**×**							
Combined medications	**×**	**×**	**×**	**×**	**×**	**×**		
Pregnancy test	**×**							
Physical examination	**×**					**×**		
Adverse event		**×**	**×**	**×**	**×**	**×**		
Serious adverse events		**×**	**×**	**×**	**×**	**×**		

BSA, body surface area; DLQI, Dermatology Life Quality Index; PASI, Psoriasis Area and Severity Index; PGA, Physician’s Global Assessment; PR-QoL, patient-reported quality of life; TCMSSS, Traditional Chinese Medicine syndrome scoring scale; VAS, visual analog scale

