**Fig. 2 Fig2:**
[figure not shown]
Different cups used for the intervention group and the control group when implementing moving cupping therapy. **a** The cups used for the intervention group can produce a negative pressure adsorption force when the air in the cup is burned. **b** The cup used for the placebo group has a special perforation design, and no negative pressure adsorption was formed after combustion

Moving cupping involves standardized manipulations. First, Vaseline is applied to the skin lesion area. Using the flashing method, a 95% ethanol-soaked cotton ball is held with tweezers and the cup is held upside-down. After the cotton ball is ignited, it is immediately moved down inside the cup and removed; the cup is then quickly placed on the skin lesion area. After using the cup to absorb the skin lesion area, the cup body is held in one hand and pushed and pulled according to the skin lesion area while applying light force, such that the skin of the treatment area turns purple. Even force is applied when pushing the cup to prevent the cup from falling off due to air leakage. This is repeated on the skin lesion area 30 times [29]. The cup is changed five times per push and pull, with an interval of no more than 10 seconds. This will be performed once every other day for 4 weeks.

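### The plan does not say that the PASI rater is blinded to allocation, contradicts itself on who knows the groups, and does not deal with cupping marks when erythema is scored

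*Protocol article*

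**What the plan says.** All places are in the protocol article.

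- **Study design** describes a "prospective, multicenter, two-arm parallel group, single-blind RCT".
- **Randomization, allocation, and blinding** says that "it is not possible to blind the operating physician involved in treatment application". It adds that "the researcher who conducts the random grouping will need to log onto the website to view the grouping situation of the participant". The concrete masking measures are a sham cup and a plan to "shield the patient’s eyes with a black opaque eye mask"; both are aimed at the patient. The section closes by saying that "the treatment plan and grouping will be known only by the statistical analyst".
- **Data collection and management** gives the scoring of everything except the patient-reported scales to trained data collectors. PASI, PGA and BSA are therefore theirs.
- **Statistical analysis** ends with "The measurer will be blinded to the results". No other sentence is about masking the rater.
- **Moving cupping intervention** describes the cup being moved over the lesion "such that the skin of the treatment area turns purple", on alternate days throughout the four treatment weeks. The perforated sham cup forms no negative pressure.
- **Primary parameters** builds PASI from erythema, scale and elevation. The primary outcome is the proportion of patients whose PASI falls by at least 75% from baseline at week 4.
- **Discussion** argues that most patients do not know how the treatment is carried out, so that "they cannot distinguish between the moving cupping placebo and moving cupping".

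**The concern.** PASI is a clinician's judgement, so the primary endpoint is only as sound as the masking of the person who makes it. The one sentence on that person names the results as what is hidden, and a rater can be kept from the results while knowing the arm. The sentence that might fill the gap, on who knows the grouping, conflicts with two other statements in its own section.

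The treatment adds a second problem. Suction leaves visible discoloration on the lesions that are being rated, and the sham does not reproduce it. This can act in two ways. A rater who recognises the marks knows the arm and may score more favourably. A rater who does not recognise them may record the colour as erythema and score less favourably. In either case the difference in PASI-75 rates no longer reflects disease alone, and no analysis can afterwards repair ratings made without masking.

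**Working it through.** **Step 1. Who knows the allocation, by role.**

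- Operating physician: knows; the article says blinding is impossible.
- Randomising researcher: knows; views the assignment on the website.
- Statistical analyst: knows; said to be the only one who does.
- Data collector who scores PASI: blinded to the results; allocation is not mentioned. Nothing says that this person is neither the operator nor the randomising researcher.
- Patient: sham cup and eye mask during the session.

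The statement that only the analyst knows is therefore contradicted twice in its own section. It also unmasks a role that could easily be masked.

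**Step 2. Can marks be present at the primary rating?** Sessions run on alternate days up to week 4, and the primary PASI is scored at week 4 on the same lesions. A rating can thus fall soon after a session. The article does not say how long marks last or how the rating is timed relative to a session.

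**Step 3. What a misread mark does to PASI.** Assumption: standard PASI scoring, with each sign graded 0 to 4 and area 0 to 6. This agrees with the stated range of 0 to 72, since 3 × 4 × 6 = 72. With area unchanged, PASI is proportional to the sum of the three signs. Take an assumed baseline of 2/2/2, sum 6.

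- One grade on one sign: 1/6 = 17% of baseline.
- Scale and elevation cleared, discoloration scored as erythema 2: 2/6 = 33% of baseline, a 67% reduction. PASI-75 is missed.
- The same with discoloration scored as erythema 1: 1/6 = 17% of baseline, an 83% reduction. PASI-75 is met.

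Whether a misread mark changes the result therefore depends on the grade given.

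**Step 4. Reproduce the planning figure.** Inputs from Sample size: 62.1% and 35.3%, two-sided 5%, power 80%.

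n = [0.621 × 0.379 + 0.353 × 0.647] / 0.268² × (1.960 + 0.842)² = 0.46375 / 0.071824 × 7.849 = 50.68, so 51 per arm as stated. With the allowance for loss, 51 × 1.2 = 61.2, stated as 61 (122 in total).

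**Step 5. Illustrate the stakes.** The documents give no size for rater bias, so shifts of 5, 10 and 15 percentage points in the cupping arm's responder rate are assumed. With d the rated difference, p̄ the mean of the two rates, se0 = √[2p̄(1 − p̄)/n] and se1 = √{[pa(1 − pa) + pb(1 − pb)]/n}:

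P(reject) = 1 − Φ[(1.96·se0 − d)/se1] + Φ[(−1.96·se0 − d)/se1]

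Example, no true effect, both arms at 35.3%, shift of 10 points, n = 51: se0 = 0.0971, se1 = 0.0966. The upper tail is 1 − Φ(0.935) = 0.175 and the lower tail 0.001, in total 0.176.

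- Type I error with 51 per arm, shifts of 5/10/15 points: 8%, 18%, 33%.
- With 61 per arm: 9%, 20%, 39%.
- With 51 per arm and an assumed common rate of 10%, since PASI-75 is harder to reach than PASI-50: 12%, 29%, 51%.
- In the other direction, marks hide 5/10/15 points of true response (62.1% against 35.3%, 51 per arm): power falls from 78% to 60%, 40%, 23%. The start is 78% and not 80% because the test here uses the pooled variance.

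**The case against.** The strongest reply is that the sentence on the measurer is loose wording. The randomisation section implies that raters are not told the arm, and the article describes a separate operating physician and trained data collectors. This stands in part. A reader might infer that the plan lets raters know the allocation, and the documents do not say so. But a sentence that is untrue for two roles is weak evidence of masking for a third, and not being told the arm does not stop a rater from seeing it on the skin.

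Three other strong readings go too far:

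- *Cupping is continued until the lesion is discoloured.* The article fixes 30 repetitions with light force; the colour is a described result, not a stopping point.
- *An unmasked analyst can steer the primary test by choosing between the t test and the Wilcoxon test.* That choice concerns quantitative variables. PASI-75 is a proportion, for which the article names the chi-square or Fisher exact test. Analyst masking is a lesser point and does not touch the rating.
- *The bias favours cupping.* Unmasking could favour it, while discoloration scored as erythema counts against it.

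It is also fair to say that the illustrations rest on chosen cases, that the shifts are assumed, and that the planning rates are PASI-50 rates while the endpoint is PASI-75. They show sensitivity and do not estimate the bias. Finally, not announcing a test of patient blinding is no error in a condensed article.

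**Conclusion.** The point holds in this form. The article names the wrong object of blinding for the PASI rater. It contradicts itself on who knows the grouping and leaves the analyst unmasked. It also describes a visible, arm-specific mark on the skin where erythema is scored for the primary endpoint, without saying how the mark is handled. This goes beyond missing detail, because the fault lies in what is stated.

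The net direction and size of the bias are unknown. The figures in the working depend on the assumed PASI grading, the 2/2/2 baseline and the assumed 5- to 15-point shifts. They show only that modest rating shifts would matter in a trial of this size. The point warrants correction because it affects the sole primary endpoint and the remedy is cheap.

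**What to change.** 1. Reconcile the randomisation section with the statistical analysis section. State that PASI, PGA and BSA are scored by a data collector who is blinded to allocation, is neither the operating physician nor the randomising researcher, and has no access to the randomisation system. List truthfully who does know the allocation.
2. Score PASI before that day's session and at a fixed interval after the previous one. Instruct raters not to score cupping discoloration as erythema.
3. Add a sensitivity analysis of week-4 PASI without the erythema item, leaving it out at baseline as well. This uses item scores already collected. It is not a standard score, so it supports the primary analysis and does not replace it.
4. Give the analyst coded groups until database lock.
5. Report as a residual limitation that a rater who is not told the arm may still see marks.

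Asking patients and raters to guess the arm is optional. The week-6 PASI is not a ready substitute for a rating free of marks: follow-up at weeks 6 and 8 is by phone, so an on-site rating would add a visit.

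The cost is revised wording, one rater instruction, one extra analysis and slightly tighter visit scheduling. Treatment and sample size do not change. Each site must confirm that its data collector is a different person from the operator and the randomising researcher, which the article does not state.
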